## Abstract

**Background:**

Main claims of the literature are that functional recovery of the paretic upper limb is mainly defined within the first month post stroke and that rehabilitation services should preferably be applied intensively and in a task-oriented way within this particular time window. EXplaining PLastICITy after stroke (acronym EXPLICIT-stroke) aims to explore the underlying mechanisms of post stroke upper limb recovery. Two randomized single blinded trials form the core of the programme, investigating the effects of early modified Constraint-Induced Movement Therapy (modified CIMT) and EMG-triggered Neuro-Muscular Stimulation (EMG-NMS) in patients with respectively a favourable or poor probability for recovery of dexterity.

**Methods/design:**

180 participants suffering from an acute, first-ever ischemic stroke will be recruited. Functional prognosis at the end of the first week post stroke is used to stratify patient into a poor prognosis group for upper limb recovery (N = 120, A2 project) and a group with a favourable prognosis (N = 60, A1 project). Both groups will be randomized to an experimental arm receiving respectively modified CIMT (favourable prognosis) or EMG-NMS (poor prognosis) for 3 weeks or to a control arm receiving usual care. Primary outcome variable will be the Action Research Arm Test (ARAT), assessed at 1,2,3,4,5, 8, 12 and 26 weeks post stroke. To study the impact of modified CIMT or EMG-NMS on stroke recovery mechanisms i.e. neuroplasticity, compensatory movements and upper limb neuromechanics, 60 patients randomly selected from projects A1 and A2 will undergo TMS, kinematical and haptic robotic measurements within a repeated measurement design. Additionally, 30 patients from the A1 project will undergo fMRI at baseline, 5 and 26 weeks post stroke.

**Conclusion:**

EXPLICIT stroke is a 5 year translational research programme which main aim is to investigate the effects of early applied intensive intervention for regaining dexterity and to explore the underlying mechanisms that are involved in regaining upper limb function after stroke. EXPLICIT-stroke will provide an answer to the key question whether therapy induced improvements are due to either a reduction of basic motor impairment by neural repair i.e. restitution of function and/or the use of behavioural compensation strategies i.e. substitution of function.

EXPLICIT is registered at the Netherlands Trial Register (NTR, ., TC 1424)

## Background

Each year, more than 32,000 patients sustain a stroke [1]. The incidence is expected to have increased by 30–45% in 2015 [2]. About 80% of the survivors have an upper limb paresis immediately after stroke onset [3], whereas only one third of all stroke patients have regained some dexterity at 6 months [4]. Recent prospective cohort studies showed that the functional outcome at 6 months is highly predictable within a critical time window of 4 weeks post stroke [4,5]. (Figure 1.)

**Figure 1 F1:**
[figure not shown]
**Probability (%) of achieving dexterity (ARAT ≥10 points) at 6 months post stroke (N = 102) starting in the first week post stroke**. Based on the Fugl Meyer scores of the flaccid arm, optimal prediction of arm function outcome at 6 months could be made within 4 weeks after onset. Patients with a favorable prognosis are presented with a red line, whereas lack of voluntary motor control of the leg in the first week with no emergence of arm synergies within 4 weeks post stroke was associated with poor outcome at 6 months (green line, [5,10]).

There is no evidence that these recovery patterns can be influenced by any specific treatment approach [6,7], though a number of studies suggest that rehabilitation should be initiated as soon as possible, preferably within the critical time window of 4 weeks post stroke [5]. In addition, treatment should be applied intensively and in a task-oriented way [4,8-10]. In particular a number of recent longitudinally conducted studies suggest that an early return of wrist and finger extension is a key factor for regaining dexterity [11-13].

Unfortunately, the underlying mechanisms responsible for recovery are not well understood [8-10,14]. A better understanding of the factors that facilitate upper limb recovery, as well as the time windows in which these recovery mechanisms work best are a prerequisite for improving our rehabilitation services in the future. Recently, several controlled trials in the chronic phase after stroke have shown that innovative therapies such as constraint-induced movement therapy (modified CIMT, [15-17]) and EMG-triggered neuromuscular electrical stimulation (EMG-NMS) [18], may improve upper limb function. So far, well designed and conducted randomized clinical trials investigating the promising effects of modified CIMT [19,20] and EMG-NMS in the acute or subacute phase after stroke are lacking. A few studies have found that improvements induced by modified CIMT [21,22] or EMG-NMS of the affected upper limb [23,24] coincide with cortical reorganizations of motor maps in patients suffering from chronic stroke. This suggests that neuroplasticity is an important mechanism for functional recovery of the upper paretic limb. However, the impact of the above-mentioned therapies on dynamics of cortical reorganization has never been investigated in stroke patients. Recent longitudinal studies also suggest that functional recovery is more than neural repair alone. For example, kinematically controlled studies showed that recovery of the paretic arm and hand strongly depends on adaptive trunk movements when distal motor deficits are present [10,25]. Therefore, understanding functional recovery of the upper limb requires not only knowledge about longitudinal changes in neuroplasticity but also about the compensation strategies patients use [10] together with changing limb neuromechanics, i.e. joint stiffness, muscle/motor function and control [26-32]. In other words, the functional impact of the time-dependent changes in cortical neuroplasticity, as well as the adaptive compensation strategies used to deal with existing motor deficits and possible neuromechanical constraints need to be explored in order to improve our knowledge about what exactly patients learn when functional improvement is observed. Therefore, the objective of the present EXPLICIT-stroke programme is to address the following research questions in the next 5 years:

(1) Is an early modified CIMT programme more effective in terms of recovery of the paretic upper limb than conventional care in stroke patients with a favourable prognosis for recovery of the upper limb? (Project A1)

(2) Is an early EMG-NMS programme for wrist and finger extensors more effective in terms of return of dexterity than conventional care in patients with initially poor prognosis for upper limb recovery? (Project A2)

(3) Are modified CIMT-induced gains reinforced by recruitment of cortical activation in the ipsilesional hemisphere when compared to usual care? (Project B1)

(4) Can improved performance of a functional reaching task be explained on the basis of behavioural compensation strategies? (Project B2)

(5) How and to what extent do wrist neuromechanical properties, i.e. stiffness, motor function and control change in the first 6 months post stroke? (Project B3)

(6) Does early intervention affect endpoint neuromechanics (Project B3)

(7) How are improvements in dexterity longitudinally related to changes observed in kinematics, neuromechanics and cortical activation (Project C).

## Methods

EXPLICIT-stroke will include 180 first ever stroke patients within five years. The study has been approved of by the Medical Ethical Reviewing Committees of the Leiden University Medical Centre (main reviewing committee: protocol number P08.035, Dutch Central Committee on Research Involving Human Subjects, CCMO, protocol number NL21396.058.08), the VU Medical Center, Amsterdam, the University Medical Centre St. Radboud, Nijmegen and the University Medical Centre Utrecht, The Netherlands.

EXPLICIT includes 3 main projects: A, B and C. The two A projects (A1 and A2) aim to investigate the effects of modified CIMT and EMG-NMS respectively, whereas the B projects aim to examine (1) the learning- and time-dependent changes in cortical neuroplasticity (project B1); 2) the kinematic changes (project B2) and 3) the neuromechanical changes (project B3) related to upper limb recovery in the first 6 months post stroke. Within project C, longitudinal, quasi-causal relationships are being sought between upper limb function improvements (A projects) and mechanisms of post stroke recovery (B projects). A schematic representation of the EXPLICIT programme is presented in Figure 2.

**Figure 2 F2:**
[figure not shown]
**Illustration of coherence between projects of EXPLICIT and subsequent phases**.

### The A projects of Explicit

The 'A' projects comprise two RCTs investigating the effectiveness of early interventions on paretic upper limb recovery in a 3-week programme starting in the second week post stroke and ending in the fourth week. In the first RCT (project A1), 60 first-ever MCA stroke patients with a National Institute of Health Stroke Score, NIHSS 1 or 2 and a voluntary extension of wrist and fingers of at least 10 degrees assessed at the end of the first week post stroke will be randomized to either an experimental group undergoing task-oriented exercises i.e. shaping procedures of the upper limb, supplemented by modified constraint-induced movement therapy (modified CIMT), or a control group. All patients will be recruited in four medical centres participating in EXPLICIT, i.e. Leiden University Medical Centre, LUMC; VU University Medical Centre, VUmc; Radboud University Medical Centre, RUMC and University Medical Centre Utrecht, UMCU.

In the second RCT (project A2), 120 patients with an initially poor prognosis for recovery of dexterity at the end of the first week, i.e. NIHSS score 3 or 4 and no voluntary control of the paretic upper limb, will be recruited and randomized either to an intervention group receiving conventional care supplemented by EMG-triggered electrotherapy (EMG-NMS) to stimulate wrist and finger extensors or to a control group.

After the intake procedure, which will include the first assessment of outcome variables, we will apply separate restricted randomization procedures (in permuted blocks) with random number tables for each participating university medical centre and for each of the projects A1 and A2. Concealed allocation will be effectuated with sealed opaque envelopes. Before randomization, patients and their families will be informed that all interventions may improve outcome, but that they will remain naive with respect to the supposed efficacy of the experimental condition to which they have been allocated. Nurses, speech therapists and social workers will continue to provide regular care depending on the patients' needs.

### Project A1

#### Background and hypotheses

Claims made in the literature are that therapy should be intensive and task-oriented and that therapy is most effective in the early stages after stroke. Two research hypotheses will be addressed in project A1: 1) Acute or subacute hemiplegic stroke patients treated for 3 weeks with an intensive daily shaping programme for the paretic upper limb will show significantly less upper extremity impairment and disability after 3 weeks compared to those patients receiving conventional training; 2) The gains achieved by modified CIMT will sustain over time, in such way that these patients will show less upper extremity deficits, and hence better outcomes in terms of dexterity at 6 months post stroke when compared to those patients who received conventional care.

#### Recruitment

Sixty subjects with a favourable prognosis will be recruited. Inclusion criteria are: 1) an upper limb deficit, i.e. a NIHSS score of 1 or 2 in the second week post stroke; 2) a first-ever ischemic lesion in the territory of the MCA, verified by CT and/or MRI scan; 3) age between 18 and 80 years; 3) written or oral informed consent; 4) be able to sit for 30 seconds without support; and 4) sufficient motivation to participate.

The exclusion criteria are 1) a pacemaker or other metallic implants; 2) upper extremity orthopaedic limitations; 3) not being able to communicate i.e. < 4 points on the Utrecht Communication Observation, UCO [33]; 4) a Mini Mental State Examination, MMSE score of 22 points or less, [8] and 5) recombinant tissue plasminogen activator (rTPA, or alteplase) treatment. There will be no restrictions with respect to age, ethnicity or socio-economic status.

#### Design and intervention

In the modified CIMT trial, patients in the experimental group will receive 30 minutes of task-oriented training of the upper extremity, aimed at improving dexterity of the paretic arm (i.e. shaping) for 5 days a week over 3 consecutive weeks. Task difficulty will be progressively increased using behavioural techniques of shaping and successive approximation [34]. In addition, the Padded Safety Mitt (Sammons Preston # 6727; Sammons Preston, Inc, Bolingbrook, IL, USA) will be applied for 2 hours to immobilize the non-paretic arm following each treatment session (excluding weekends). During toileting and under other circumstances that require safe balance, patients will be allowed to remove the padded safety mitt. The content and duration of the modified CIMT therapy as well as the shaping exercises will be recorded in a patients' log reflecting different treatment goals. Conventional care will consist of exercise therapy based on the principles of the NDT concept for a restricted one-by-one intervention time of 30 minutes per working day, 5 days a week for 3 consecutive weeks excluding weekends. Content and daily duration of conventional therapy will be recorded in the patient logs using different treatment codes for exercise intervention types and intervention goals (See for example Kwakkel et al [8]). The modified CIMT programme is focused on regaining voluntary wrist and finger extension of the paretic hand by intensive exercise therapy 2 times a day 30 minutes for 3 weeks. The protocol for modified CIMT is available at .

All therapy sessions will be individually applied by a local trained physical therapist (PT) and/or occupational therapist (OT) working in one of the participating university medical centres, or, if a patient is discharged earlier, in a regional rehabilitation centre.

After 3 weeks, the intensity of the interventions implemented by the OTs and PTs will be standardized in both arms of project A1 and restricted to exercise therapy alone, given for a maximum of 30 minutes per working day. Duration and aims of interventions implemented by PTs or OTs will be monitored by means of monthly phone calls by the local member of the project staff at the university medical centre.

#### Power analysis of project A1

Analysis is based on a statistical power of 80% with an alpha of 5% for detecting a meaningful difference of 6 points i.e. 10% on the Action Research Arm Test, ARAT sum score as the primary outcome measure [35]. The estimated population variance is based on the outcome of a randomized clinical trial in 102 stroke patients with a first-ever MCA stroke i.e. a standard deviation of 8 points measured with ARAT at 2 weeks post stroke [5,8]. Controlling for dependency (test-retest reliability of 0.9 for ARAT based on 5 repeated measurements in the first 5 weeks), a sample-size of 60 patients including 10% drop outs should be sufficient.

### Project A2

#### Background and hypotheses

Patients with a poor prognosis for functional recovery (estimated to include about 2/3 of all stroke patients with a MCA stroke) will undergo an intensive stimulation programme of wrist and finger extensors using EMG-triggered neuromuscular stimulation (EMG-NMS). These patients are unable to move their paretic upper limb voluntarily. Return of voluntary motor control can so far only be facilitated by somatosensory input and imaginary movement. The assumed positive impact of EMG-NMS is based on the finding that 2 hours of sensory stimulation of the median nerve of a paretic limb may result in improved pinch strength [23]. This improvement in muscle strength correlates with the stimulus intensity and has been identified in the absence of motor training. Virtual imaging has also been found to improve cortical plasticity and motor performance of the upper limb in chronic stroke [24]. The above results suggest that somatosensory stimulation, combined with virtual imaging by applying EMG-NMS, may be a promising adjuvant therapy to initiate active motor control in stroke patients with an upper limb deficit. It is hypothesized that cortical ipsi-lesional and contra-lesional plasticity is facilitated by EMG-NMS of wrist and finger extensors especially early after stroke, when the outcome in terms of dexterity has not yet been defined, hence increasing the probability of return of some functional dexterity [24]. In addition, it is believed that the movement imagery component causes neural networks in the motor cortex, associated with the specific imagined movement, to be stimulated and reinforced. Evidence supporting this theory has been found using fMRI [24]. Based on this 'use it or lose it' principle [36-38], one may assume that a higher percentage of patients in the experimental group will regain some dexterity in terms of ARAT scores, i.e. > 9 points [5], when compared to the control group. If triggering with the paretic limb proves to be not possible, EMG activity of the non-paretic wrist and fingers extensors will be used to trigger activation of the paretic limb, since ipsilateral activation is also known to reinforce cortical activity in the affected hemisphere after stroke [39].

#### Recruitment for project A2

A total of 120 subjects with a first-ever MCA stroke and an initially poor prognosis for recovery of dexterity (NIHSS score 3 and 4) in the second week post stroke will be recruited. Inclusion and exclusion criteria will be identical as for project A1.

#### Design and intervention of project A2

In the second week post stroke, patients with an initially poor functional prognosis who have been allocated to the control group will engage in passive range-of-motion exercise and facilitation of voluntary movements for 30 minutes per week day, whereas the experimental group will receive EMG-triggered NMS (Stiwell Med 4, Otto Bock Healthcare Products GmbH, Vienna, Austria) of wrist and finger extensors each day for 3 periods of 30 minutes per working day during 3 consecutive weeks. The cyclic stimulation will be biphasic, with a pulse width of 200 μsec and intensity up to 29 mA with a frequency of 50 Hz. Patients are asked to imagine the dorsiflexing movement of fingers and wrist on the paretic side. This causes some initial muscle activity which, when detected by the EMG electrodes, amplified and presented once again to the muscle, may elicit a genuine contraction of the wrist extensors [40]. For those patients showing no EMG activity, the extensors of the non-paretic hand will be used as a trigger to activate the paretic hand. This new mode of electrical stimulation has been claimed to be superior to other types of electrical stimulation programme [18,40]. Finally, patients may learn to facilitate extensor activitity of wrist and fingers by simultaneously abducting their paretic arm (often described as Soques phenomenon). Details of the EMG-NMS treatment protocol is available at .

The intensity and content of the EMG-NMS as well as other therapies applied will be recorded in a patient log-book. Both groups will receive usual care in terms of lower limb training. After 3 weeks, usual care will be restricted to a maximum of 30 minutes of upper limb practice, monitored by monthly phone calls by the project staff. All therapy sessions will be individually applied by local physical (PT) and/or occupational (OT) therapists working at the local setting (UMC and local rehabilitation centre) where patients have been admitted. For this latter purpose, PTs and OTs who participate in EXPLICIT will have a training course in the preparation phase.

#### Power analysis for project A2

Based on a previous cohort study with 101 first-ever MCA strokes [8], patients with a poor prognosis have a probability of about 6% to regain some dexterity (ARAT > 9 points) at 6 months post stroke [8]. In project A2 we assume a proportional difference of 12% in favour of the experimental group. Based on a statistical power of 80% with an alpha of 5% and a test-retest reliability of 0.9 for ARAT with 5 repeated measurements, 120 patients should be enough to show statistical significance in favour of EMG-NMS in the poor prognosis group.

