#### Outcome variables of projects A1 and A2

Primary outcome variable for both A1 and A2 projects will be the Action Research Arm test score (ARAT). Secondary outcome variables are the scores of: Motricity Index (MI) of arm and leg, Fugl-Meyer for the arm (FM-arm), Erasmus modification of the Nottingham Sensory Assessment (EmNSA), Letter Cancellation Task (LCT), Nine Hole Peg test (NHPT), a structured participant interview of real arm use using the Motor Activity Log (MAL), Stroke Impact Scale (SIS version 3.0) and Nottingham Extended ADL (NEADL). With the exception of the NEADL and SIS, all assessments will be applied to all 180 patients weekly in the first 5 weeks post stroke. Subsequently, follow-up assessments will be made at 8, 12 and 26 weeks after stroke.

The ARAT test is a performance test which assesses the ability to perform gross movements and the ability to grasp, move and release objects differing in size, weight and shape [41]. The original test consists of 19 items, rated on 4-point ordinal scales (0 to 3). By removing 4 items, a hierarchical 1-dimensional scale has been constructed [42]. The ARA test has been shown to be valid, reliable and responsive [35]. The minimal clinically important difference (MCID) will be set at about 10% of the range of the scale, i.e. 6 points [15]. For project A2, return of dexterity will be defined as 10 points or more on the ARAT [5].

The Motricity index (MI) reliably and validly assesses the presence of paresis in stroke patients by testing 6 functions rated from 0 to 100 points for each limb [8,43].

The FM-arm score is a reliable and valid motor performance test [44,45] and evaluates the ability to make movements outside the synergistic pattern.

A translated and adapted version of the MAL will be used [46] which contains the 14 original activities, 11 additional activities, and 1 optional activity chosen by the patient. Reliability and validity of the MAL has been proved in a number of studies [46]. The MAL will be administered to each applicant and, if available, their caregivers. It will be used to independently rate how well (11-point Quality of Movement [QOM] scale) and how much (11-point amount-of-use [AOU] scale) the paretic arm was used spontaneously to accomplish 30 activities of daily living outside the laboratory [47].

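### Project A2: the stated inputs (6% versus 18% regaining dexterity) give about 54% power with 120 patients in a two-sided test, or about 67% one-sided, not the stated 80%

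*Protocol article*

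**What the plan says.** The section on the power analysis for project A2 starts from an earlier cohort, in which "patients with a poor prognosis have a probability of about 6% to regain some dexterity (ARAT > 9 points) at 6 months post stroke". It continues: "In project A2 we assume a proportional difference of 12% in favour of the experimental group". With 80% power, alpha 5% and "a test-retest reliability of 0.9 for ARAT with 5 repeated measurements", it concludes that "120 patients should be enough to show statistical significance in favour of EMG-NMS in the poor prognosis group". It gives no formula, does not say whether the test is one- or two-sided, and does not say whether 12% is absolute or relative.

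The section on outcome variables names the ARAT score as primary for both A projects and adds the dichotomy for A2: "For project A2, return of dexterity will be defined as 10 points or more on the ARAT". ARAT is assessed weekly for the first five weeks and again at 8, 12 and 26 weeks. On allocation, the section on the A projects says that "we will apply separate restricted randomization procedures (in permuted blocks) with random number tables" for each centre and project. It gives no ratio.

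**The concern.** A rise from 6% to 18% is a 12-point difference in a fairly rare binary outcome, and 60 patients per arm is small for that at 80% power. The only input that might make up the shortfall is the reliability clause. Such a clause belongs to the analysis of a continuous score measured repeatedly, whereas the effect size here is a proportion at 6 months.

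A2 holds 120 of the programme's 180 patients and answers its second research question. If the true power is near one half, the trial would miss the effect it was built to detect almost as often as it would find it. Anyone relying on the printed 80% would then give a non-significant result more weight than it can bear.

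**Working it through.** **Inputs from the article.** Control proportion 0.06; difference 0.12; power 80%; alpha 5%; total 120; reliability 0.9 with 5 measurements.

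**Assumptions.** The difference is absolute (0.06 versus 0.18). Allocation is 1:1, so 60 per arm. There is a single comparison of two proportions at 6 months. Sidedness is not stated, so both are shown.

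**Step 1: try to reproduce 120.** The pooled-variance formula per arm is

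n = [z_α·√(2·p̄(1−p̄)) + z_β·√(p₁(1−p₁) + p₂(1−p₂))]² / (p₂−p₁)²

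with p̄ = 0.12, √(2 × 0.12 × 0.88) = 0.4596 and √(0.06 × 0.94 + 0.18 × 0.82) = 0.4517.

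- Two-sided: (1.960 × 0.4596 + 0.8416 × 0.4517)² / 0.0144 = 113.9, so 114 per arm and 228 in total.
- One-sided: (1.645 × 0.4596 + 0.8416 × 0.4517)² / 0.0144 = 89.6, so 90 per arm and 180 in total.

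Other two-sided methods give totals of 224 (unpooled), 216 (arcsine) and 262 (continuity-corrected). None is near 120, which is about 53% of 228.

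**Step 2: power with 60 per arm, 6% versus 18%.**

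| Method | Two-sided 5% | One-sided 5% |
|---|---|---|
| Pooled normal formula | 52.5% | 65.0% |
| Unpooled normal formula | 53.9% | 66.0% |
| Arcsine | 55.1% | 67.1% |
| Chi-square, uncorrected, full enumeration of both binomials | 53.7% | 66.7% |
| Fisher's exact test, full enumeration | 42.2% | 57.0% |

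**Step 3: the reliability clause.**

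- Read as the mean of five equally correlated measurements, the variance factor is (1 + 4 × 0.9)/5 = 0.92. Then 114 × 0.92 = 104.9, so 105 per arm and 210 in total two-sided. One-sided it is 90 × 0.92 = 82.8, so 83 per arm and 166 in total. Power at 120 becomes 56.0% or 68.2%. With correlation 0.9 this factor cannot fall below 0.90 however many measurements are taken, while 120/228 = 0.53 would be needed.
- Read as adjustment for a baseline correlated 0.9 with outcome, the factor is 1 − 0.9² = 0.19, and 114 × 0.19 = 21.7, so about 44 patients in total. That overshoots in the other direction.

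**Step 4: other readings of 12%.** If it means 6% versus 12%, power with 60 per arm is 21%. If it means a relative increase of 12% (6% to 6.72%), power is about 4%. The absolute reading is the one most favourable to the stated number.

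**Step 5: figures for a restatement.** By the enumerated two-sided chi-square test with 60 per arm, power is 77.8% at 6% versus 23% and 81.4% at 6% versus 24%. The detectable difference at 80% power is therefore about 18 points. If 10% of patients were lost (54 per arm), power for 6% versus 18% would be 49.4%. The 10% is taken from project A1 as a sensitivity value only.

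**Step 6: what a non-significant result could show.** If both arms had 4 of 60 responders, the Newcombe 95% interval for the difference would run from −10.1 to +10.1 points, which excludes 12. Over all outcomes at a true 6% in both arms, the Newcombe interval excludes +12 points with probability 0.68. Around an observed 12-point difference, by contrast, the half-width is 1.96 × √[(0.06 × 0.94 + 0.18 × 0.82)/60] = 11.4 points.

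**The case against.** The strongest reply is that the primary outcome is the ARAT score, assessed eight times, and that the reliability clause points to a repeated-measures analysis that could be more powerful than one comparison at 6 months. The analysis model for A2 is indeed not shown, and the dexterity cut-off is defined without a time point. This limits the finding to the comparison that the calculation itself describes. It does not rescue the 80%: the section gives no mean difference or standard deviation for A2, and its only effect size is a proportion set against a 6-month rate. Nor can one say that a repeated-measures argument is impossible in principle. What can be said is that its use here is unexplained and that neither reading tried gives 120.

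The aim is also worded in one direction, so a one-sided test may have been meant. Power is then about 67%, still well short.

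Two stronger readings are tempting. One is that any null result from A2 would be uninformative. Step 6 shows otherwise: when the arms come out nearly equal, the interval will often exclude 12 points. The other is that A2 wrongly lacks a drop-out allowance. The article does not say whether 120 already includes losses, and a condensed article's silence on that is not an error.

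**Conclusion.** The point holds as an arithmetic mismatch within one paragraph: the printed inputs and the printed sample size do not agree. For 6% versus 18% with 60 per arm, power is about 54% two-sided (42% with Fisher's exact test) or about 67% one-sided, against a stated 80%. The required total is about 228 or 180. This rests on the absolute reading of 12%, 1:1 allocation and a single two-proportion comparison at 6 months. The gap is far larger than any choice of formula can explain. It does not follow that a non-significant result would always be inconclusive; that depends on where the confidence interval lies.

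**What to change.** In the A2 power analysis:

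1. State that the 12% is an absolute difference (6% versus 18%), and state the sidedness of the test and the allocation ratio.
2. Remove the reliability and repeated-measurements clause from this calculation, or give the formula and the analysis that justify it.
3. Restate the power as about 54% two-sided with 120 evaluable patients (about 49% if 10% are lost). Alternatively, keep 80% and state the detectable difference, about 6% versus 24%.
4. State in advance that the A2 dexterity result will be reported as a risk difference with its 95% confidence interval, and that a non-significant result will be called inconclusive only if the interval still includes the assumed 12-point difference.

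The cost is protocol wording and a less favourable power statement. No extra patients are needed for these changes, but they do not raise the power. Reaching 80% for the assumed effect would take about 228 patients two-sided.
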